# Improving office workers’ mental health and cognition: a 3-arm cluster randomized controlled trial targeting physical activity and sedentary behavior in multi-component interventions

**DOI:** 10.1186/s12889-019-6589-4

**Published:** 2019-03-05

**Keywords:** Office workers, Work place, Randomized intervention, Sedentary behavior, Physical activity, Accelerometer, Mental health, Cognition

## Abstract

**Background:**

Physically inactive and sedentary lifestyles are negatively related to both mental health and cognition. For office-workers, who spend two-thirds of their workday sitting, it is important to improve these lifestyles. The aim of this study is to assess the effectiveness of multi-component interventions, incorporating individual, environmental and organizational changes, to increase physical activity or reduce sedentary behavior among office-workers in order to improve mental health and cognition.

**Methods:**

a 3-arm, clustered randomized controlled trial (RCT) with waiting list control group amongst adult office-workers of two large Swedish companies. Cluster teams will be randomized into 6-month interventions or to a passive waiting list control group which will receive the allocated intervention with a 6-month delay. Two multicomponent interventions will be studied of which one focuses on improving physical activity and the other on reducing sedentary behavior. Both interventions include 5 sessions of motivational counselling. In the physical activity intervention persons also get access to a gym and team leaders will organize lunch walks and encourage to exercise. In the sedentary behavior intervention standing- and walking meetings will be implemented and team leaders will encourage to reduce sitting. The recruitment target is 110 office-workers per arm (330 in total). Measurements will be repeated every 6 months for a total intended duration of 24 months. Proximal main outcomes are physical activity measured with accelerometers and sedentary behavior with inclinometers. Distal outcomes are self-reported mental health and a cognition test battery. Additional outcomes will include cardiovascular fitness, body composition, sleep, self-reported physical activity and sedentary behavior, other health habits, physical health, and working mechanisms from blood samples and questionnaires.

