### Study population

Office workers from two Swedish companies (Intrum and ICA-gruppen) will be invited to participate in the study, with the target to include a total of 330 persons. At Intrum, persons will be recruited both working in Stockholm and in Göteborg, with respectively 168 and 265 employees. ICA-gruppen is a large company in Stockholm of around 1600 employees.

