### Randomization

In order to control contamination and to limit interaction between the different groups, randomisation will be done on a cluster level. We aim to have 24 clusters (8 clusters per arm), 10 at Intrum and 14 at ICA-gruppen. Clusters will be composed while considering: 1) having a team or line manager, 2) having regular group meetings, 3) limited regular meetings with other teams. Block randomisation and assignment will be performed using a computer-generated random number list. Groups will be randomly allocated (1:1) with stratification for company and cluster size (large vs small). In order to implement the interventions in an order consistent with logistical capacity matched randomization will be used in case needed. Randomization will be performed after finishing first data collection and participants will be notified by email. Randomization and allocation will be performed by researchers not involved in data collection. Research assistants involved in data collection and processing will be blinded for group allocation.

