### Sample size

Sample size was calculated in three steps [67]:i.Sample size based on an individualized randomized controlled trialii.Corrected for the design effect, taking into account the clusteringiii.Corrected for unavailable data

The sample size calculation was based on 1 follow-up measurement, with a power of 80% and significance level of 0.05, corrected for 3 groups (0.05/3 = 0.017).

The design effect was 1.77. This was determined, assuming that the proportion of variance accounted for by between cluster variations was 0.05 [68]. Furthermore, we corrected for unequal clusters, assuming an average cluster size of 14 with a standard deviation of 5.83.

Unavailable data were assumed by correcting for the drop out of 3 clusters, with an average cluster size of 14 per group and for unavailability of data (missing, individual drop-outs) for 20% of participants.

For the remaining input of the sample size calculations, data were used from subproject 1 of the larger research project (as described earlier).

Using these input, estimated needed sample sizes are the following:Physical activity, moderate to vigorous physical activity, meeting the guidelines

Proportion of participants meeting guidelines in control group: 30%.

Estimated proportion of participants meeting guidelines in intervention groups: 60%.i.*Sample size based on individualized randomization:* 52 per groupii.*Corrected for design effect:* 92 per groupiii.*Corrected for unavailable data:* 125 per groupSedentary behavior, total sedentary behavior, in hrs/day

Difference in mean value between groups: 1 h/day.

Standard deviation: 1.4 h/day.i.*Sample size based on individualized randomization:* 41 per groupii.*Corrected for design effect:* 72 per groupiii.*Corrected for unavailable data:* 101 per groupMental health, stress, single item [24]

Proportion of participants with stress complaints in control group: 26%.

Estimated proportion of participants with stress complaints in intervention groups: 5%.i.*Sample size based on individualized randomization:* 57 per groupii.*Corrected for design effect:* 100 per groupiii.*Corrected for unavailable data:* 134 per groupCognition, stroop test (in seconds)

Difference in mean value between groups: 7 s.

Standard deviation: 9.85 s.i.*Sample size based on individualized randomization:* 41 per groupii.*Corrected for design effect:* 73 per groupiii.*Corrected for unavailable data:* 102 per group

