### Statistical analyses

In accordance with the research questions, statistical analyses will be conducted to determine whether the groups differ in changes over time in proximal, distal as well as secondary outcomes. Statistical significance will be set at the 5% level (two-tailed). To adjust for company and clustering, analyses will be performed using multilevel modelling. The models will include allocated group (reference group = control group) and baseline values. Both crude models and models adjusted for potential confounders will be determined. Potential confounders will be defined a priori based on the findings from the larger research project. Separate models will be made for the different outcomes regarding physical activity, sedentary behavior, mental health and cognition. All analyses will be performed using both per protocol and intention to treat approaches, were intention to treat is defined as persons attending at least 3 out of 5 counselling sessions.

Moderator analysis will examine whether intervention effects differ across individual (e.g. age, gender and education). Mediator analyses will test whether individual and organizational factors, described under working mechanisms, mediated the intervention effects.

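### The target of 110 per arm is below the plan's own requirement for activity guidelines (125) and stress (134) at 80% power and alpha 0.017, and the shortfall is not acknowledged

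*Protocol article*

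**What the plan says.** The abstract fixes the size of the trial: "The recruitment target is 110 office-workers per arm (330 in total"). The Study population section repeats it, "with the target to include a total of 330 persons". The Randomization section gives the structure: "We aim to have 24 clusters (8 clusters per arm), 10 at Intrum and 14 at ICA-gruppen".

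The Sample size section plans on one follow-up measurement "with a power of 80% and significance level of 0.05, corrected for 3 groups (0.05/3 = 0.017"). It derives a final requirement per group for four outcomes: 125 for meeting the activity guidelines, 101 for sedentary time, 134 for stress and 102 for Stroop. The Statistical analyses section uses a different level: "Statistical significance will be set at the 5% level (two-tailed"), with no correction mentioned.

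**The concern.** Two of the four requirements exceed the target, by 15 per arm (125 - 110) and 24 per arm (134 - 110). The article neither explains why 110 was chosen nor says that the 80% is given up for these outcomes.

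Physical activity is one of the two proximal main outcomes and part of the primary hypothesis. Stress is the only mental-health outcome that was sized. Someone who reads a null result on either would take it as coming from a trial with 80% power at the corrected alpha, which the plan's own figures do not support.

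**Working it through.** **Inputs, all from the Sample size section.** Alpha 0.05/3 and power 80%. Between-cluster variance share: "assuming that the proportion of variance accounted for by between cluster variations was 0.05". Cluster size: "assuming an average cluster size of 14 with a standard deviation of 5.83". Losses: three clusters of 14, and 20% of participants. Effects: 30% vs 60% (guidelines), 26% vs 5% (stress), 1 h/day with SD 1.4 (sedentary time), 7 s with SD 9.85 (Stroop). Two-sided testing is taken from the Statistical analyses section and equal arms from the Randomization section.

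**Reproducing the plan.**
- Step i: (2.394 + 0.842)² = 10.469. With unpooled variances, guidelines: (0.21 + 0.24) × 10.469 / 0.30² = 52.3 (stated 52). Stress: (0.1924 + 0.0475) × 10.469 / 0.21² = 57.0 (stated 57). Means: 2 × 10.469 × (1.4/1)² = 41.0 and 2 × 10.469 × (9.85/7)² = 41.5 (both stated 41).
- Step ii: CV = 5.83/14; design effect 1 + [(CV² + 1) × 14 - 1] × 0.05 = 1.771 (stated 1.77). Then 52 × 1.77 = 92.0 (stated 92) and 57 × 1.77 = 100.9 (stated 100).
- Step iii: n × 1.2 + 14, applied to the stated 92, 72, 100 and 73, gives 124.4, 100.4, 134.0 and 101.6. Rounded up, these are the printed 125, 101, 134 and 102.

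So 125 and 134 are genuine results of the plan's method, not misprints. The loss of three clusters has to be read as one cluster of 14 per group; of the readings tried, only this one returns all four figures.

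**Power at 110 per arm.** Evaluable per arm: (110 - 14) × 0.8 = 76.8, or (110 - 14)/1.2 = 80 under the plan's ×1.2 rule. Effective n: 76.8/1.77 = 43.4, or 80/1.77 = 45.2. Power = Φ(difference/SE - 2.394). For guidelines at 43.4: 0.30/√(0.45/43.4) = 2.946, and Φ(0.552) = 0.709. For stress: 0.21/√(0.2399/43.4) = 2.824, and Φ(0.430) = 0.666.

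Each range below runs from 76.8 to 80 evaluable, at alpha 0.017. The t column uses a noncentral t with 18 df (21 remaining clusters minus 3 arms).

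| Outcome | Normal quantiles | t, 18 df |
|---|---|---|
| Activity guidelines | 71-73% | 62-65% |
| Stress | 67-69% | 58-60% |
| Sedentary time | 82-84% | 75-77% |
| Stroop | 82-84% | 74-76% |

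**Sensitivity to the design effect.** After 20% individual loss the mean cluster size is 14 × 0.8 = 11.2, and the same formula with the same CV gives 1.61. With 76.8 evaluable, in the order of the table, power is 76%, 72%, 86% and 86% with normal quantiles and 67%, 63%, 79% and 79% with t. Guidelines and stress stay below 80% either way.

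**At alpha 0.05** (76.8 evaluable, design effect 1.77), guidelines and stress reach 84% and 81% with normal quantiles, and 80% and 76% with t on 18 df.

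**The case against.** The strongest reply is that the analysis is set at 5%, and at that level 110 per arm gives roughly 80% or more for both outcomes with normal quantiles. This stands as a limit on the point. A reader might infer that the trial is underpowered for physical activity and stress at whatever level it is tested; the documents do not support that. It does not remove the contradiction, because the plan ties its 80% to 0.017, and relying on 0.05 means dropping the three-group correction.

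A second reply is that the models include baseline values, which the sizing does not count. If variance falls by 1 - r², 80% at 0.017 with normal quantiles needs r of about 0.41 for guidelines (√[1 - (2.946/3.236)²]) and 0.49 for stress (√[1 - (2.824/3.236)²]). Such correlations are possible, but the article gives none.

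Third, 8 × 14 = 112 per arm may explain the choice of 110. That is plausible, but it is not offered as a reason, and it does not change what 110 delivers.

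The t column also invites the inference that none of the four outcomes reaches 80%. That goes too far. The article does not say which quantiles it used, normal quantiles reproduce its figures, and with the design effect recalculated for smaller clusters sedentary time and Stroop come to 79% even with t. The small number of clusters is a secondary matter; the gap between 110 and 125 or 134 does not depend on it.

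**Conclusion.** The point holds at the planning alpha. The target is 15 per arm short of the plan's own requirement for guideline attainment (12% of 125) and 24 short for stress (18% of 134), and the article does not acknowledge this. The 80% tied to alpha 0.017 is not delivered for these two outcomes and is delivered for the other two on the plan's own method.

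The power figures assume one lost cluster of 14 per arm, 20% individual loss, unpooled variances and no gain from baseline adjustment. The remaining uncertainty is which alpha governs the trial, since the Sample size and Statistical analyses sections disagree.

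**What to change.** In the Sample size section, state the power that 110 per arm gives for each of the four outcomes, naming the alpha and the quantiles used, and say plainly that 80% at 0.017 is not met for guideline attainment or stress. In the same revision, reconcile 0.017 with the 5% level in the Statistical analyses section: either carry the three-group correction into the analysis, or drop it from the sizing and quote power at 0.05 on that basis.

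The cost is a few sentences and a less favourable power statement; no extra recruitment is needed. Raising the target to 134 per arm (402 in total) would also resolve the conflict, but the Data collection section planned inclusion to end in December 2018 and the article appeared in March 2019.

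Making baseline-adjusted continuous moderate-to-vigorous activity the powered activity outcome is an option only. It changes the outcome hierarchy and would need a standard deviation from subproject 1, which the article does not give.

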**Discussion:**

This cluster RCT will contribute to the currently available evidence by comparing the effectiveness of multi-component interventions targeting physical activity or sedentary behavior with the end goal of improving mental health and cognition. This study is strong in its cluster randomized design, numerous objective outcome measures and long-term follow-up. The exact content of the interventions has been defined by combining theory with results from a larger research project as well as having a continuous dialogue with the involved companies.

**Trial registration:**

ISRCTN92968402.

**Electronic supplementary material:**

The online version of this article (10.1186/s12889-019-6589-4) contains supplementary material, which is available to authorized users.

## Background

Physically inactive and sedentary lifestyles are major public health problems with accumulating evidence that these lifestyles are related to increased risk of cardio metabolic health and premature mortality [1–3]. A substantial proportion of life is spent at work and ever more people have office jobs in which sitting is the default [1]. Epidemiological studies report that office workers spend at least two-thirds of their workday sitting [4, 5]. Office-workers are therefore an important target group for interventions to improve physical activity or reduce sedentary behavior.

Healthy brain functions is an umbrella term which includes mental health and cognition. To maintain healthy brain functions, the brain requires a constant supply of oxygen and other chemicals, delivered via its abundant blood vessels. Physical activity helps to circulate nutrient-rich blood efficiently throughout the body to keep the blood vessels healthy and it increases the creation of mitochondria both in our muscles and in our brain [6]. Furthermore, physical activity might enhance neurogenesis: the ability to grow new brain cells [7]. Sedentary behavior has been consistently found to be related to worse cognitive performance [8], and there is increasing evidence that physical inactivity affects several physiological mechanisms underpinning brain health with negative consequences on cognition and mental health [9–11].

These identified links of physical activity and sedentary behavior with cognition and mental health have led to our hypotheses that increasing physical activity or reducing sedentary behavior will result in better mental health and cognition. So far only few studies have looked into this. A pilot investigation among high school students studied the effects of the implementation of stand-biased school desks on brain functions, and found that continued utilization of these desks was associated with significant improvements in executive function and working memory capabilities [12]. However, another study found no-long term effects of a physical activity intervention in preadolescents on working memory or arithmetic [13]. Further controlled intervention studies clarifying this relation in population groups at risk, such as office-workers, are therefore warranted.

As it is unknown whether sedentary behavior or physical activity could have the greatest impact on mental health and cognition, it is important to compare separate interventions on physical activity and sedentary behavior to a group receiving no intervention. Physical activity interventions have shown mixed effects on improving physical activity, with some interventions succeeding in certain subgroups, resulting in an improvement of selected health outcomes, work culture, and job stress [14]. Workplace interventions aiming at reducing sedentary behavior also show inconsistent results, and it therefore remains unknown which types of interventions and delivery mode should be advised to reduce sedentary behavior [15]. For both physical activity and sedentary behaviour, there is still a lack of well conducted intervention studies among office-workers, especially with long-term follow-up of objectively measured physical activity patterns combined with brain functions outcomes [15, 16].

This study is the third subproject of a research project entitled “Physical activity and healthy brain functions”. The first subproject is a cross-sectional study among 547 office-workers to identify how different components within objectively measured physical activity patterns are associated to healthy brain functions such as mental health and cognitive function. The second subproject aims at understanding the possible mechanisms of how physical activity behaviors might promote healthy brain functions. This is achieved by investigating acute effects of three different, highly standardized but also ecologically valid types of working day physical activity patterns on brain functions. Results and data of the first parts of this project have been used in the development of the current trial; in particular for the sample size calculations and the development of the interventions [17].

## Methods

### Aim

The aim of this study is to assess the effectiveness of multi-component interventions, incorporating individual, environmental and organizational changes, to increase physical activity or reduce sedentary behavior among office-workers in order to improve mental health and cognition.

### Research questions

For inactive and sedentary office workers, does a multi-component intervention to promote physical activity or reduce sedentary behavior lead to more favorable physical activity and sedentary behavior?Do favorable changes in physical activity or sedentary behavior result in better mental health and cognition, on the short and long term?

The primary hypothesis is that the multi-component interventions will favorably change office-workers physical activity or sedentary behavior as compared to the waiting list control group at 6 months. The secondary hypothesis is that these changes in physical activity patterns will in turn have positive longer term effects on mental health and cognition.

### Trial registration

The trial was prospectively registered as ISRCTN92968402 on 27/02/2018, recruitment started 15/03/2018. Note that only because the date of the invoice for registration of trial was set and therefore paid after recruitment registration, ISRCTN has flagged the trial as retrospectively. However an editorial note has been added to the trial registration to clarify that by scientific definition, our trial was registered prospectively, i.e. a final version of the trial registration was received and approved by ISRCTN before the start of recruitment.

### Design

The design is a 3-armed, clustered randomized controlled trial with waiting list control group, see Fig. 1. This 24-months study includes 5 assessment points. The outcomes of the randomized controlled trial are based on the first two measurement points. After that, the study continues as a cohort study with long term follow-up measurements of up to 1.5 years after the end of the intervention.

**Fig. 1 Fig1:**
[figure not shown]
The 3 arms, with the 5 specified measurement points

### Study population

Office workers from two Swedish companies (Intrum and ICA-gruppen) will be invited to participate in the study, with the target to include a total of 330 persons. At Intrum, persons will be recruited both working in Stockholm and in Göteborg, with respectively 168 and 265 employees. ICA-gruppen is a large company in Stockholm of around 1600 employees.

### In- and exclusion criteria

Inclusion criteria:Aged between 18 and 70 years of ageHave the capability of standing and exercising

Exclusion criteria:Not be working for the full duration of the first study year (i.e. retirement, maternity leave)Very high physical activity level: more than 30 min/day in prolonged bouts (≥10 min) moderate to vigorous physical activity. This exclusion criteria will be checked by analyzing accelerometer data. Note that because subproject 1 has shown that almost all office-workers reported high levels of sedentary behavior [17], sedentary behavior will not be used as an exclusion criterion. Data collected of these persons will be excluded from the analytical sample

### Recruitment

Information meetings about the aim of the project and the research questions will be held at personnel meetings by the researchers. Furthermore, a short video will be spread on the internal webpages of the companies. Invitations to participate will be send by email and subjects can sign up online. If they thereafter chose to participate in the study, they will be assessed on eligibility.

### Randomization

In order to control contamination and to limit interaction between the different groups, randomisation will be done on a cluster level. We aim to have 24 clusters (8 clusters per arm), 10 at Intrum and 14 at ICA-gruppen. Clusters will be composed while considering: 1) having a team or line manager, 2) having regular group meetings, 3) limited regular meetings with other teams. Block randomisation and assignment will be performed using a computer-generated random number list. Groups will be randomly allocated (1:1) with stratification for company and cluster size (large vs small). In order to implement the interventions in an order consistent with logistical capacity matched randomization will be used in case needed. Randomization will be performed after finishing first data collection and participants will be notified by email. Randomization and allocation will be performed by researchers not involved in data collection. Research assistants involved in data collection and processing will be blinded for group allocation.

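### The stated 80% power at the 0.017 level uses normal quantiles; with about 7 clusters per arm it is about 71-72% before any credit for baseline adjustment

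*Protocol article*

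**What the plan says.** All places are in the protocol article.

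- **Randomization:** "We aim to have 24 clusters (8 clusters per arm". Allocation is by cluster, stratified by company and cluster size.
- **Sample size, level and power:** the sizes are computed "with a power of 80% and significance level of 0.05, corrected for 3 groups (0.05/3 = 0.017").
- **Sample size, clustering:** "The design effect was 1.77", "assuming that the proportion of variance accounted for by between cluster variations was 0.05", with a mean cluster size of 14 and an SD of 5.83.
- **Sample size, losses:** "Unavailable data were assumed by correcting for the drop out of 3 clusters, with an average cluster size of 14 per group", plus 20% unavailable individual data.
- **Sample size, results per group** (individual / after design effect / after losses): physical activity 52/92/125, sedentary behaviour 41/72/101, stress 57/100/134, Stroop 41/73/102. The Abstract sets the target at 110 per arm.
- **Statistical analyses:** "analyses will be performed using multilevel modelling", with allocated group (control as reference) and baseline values in the model. Also: "Statistical significance will be set at the 5% level (two-tailed"). No division by 3 is stated there.

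**The concern.** A design effect enlarges the variance of the treatment contrast to allow for clustering. It does not allow for the fact that the between-cluster variation has to be estimated from few clusters. With some 20 clusters, the reference distribution for the treatment effect is closer to a t-distribution with fewer than 20 degrees of freedom than to a normal. None of the three listed sizing steps contains a term for this.

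At stake is whether the printed 80% power at 0.017 is true for the planned number of clusters. If the final test respects the cluster count, power is lower than stated. If it ignores the count, the false-positive rate is higher than stated.

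**Working it through.** **1. Reproducing the plan's sizes.** Two-sided alpha 0.05/3 gives z = 2.394; 80% power gives z = 0.842; the squared sum is 10.469.

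- Means, n = 2 × 10.469 × (SD/difference)²: sitting (1.4/1) 41.04; Stroop (9.85/7) 41.46. Stated: 41 and 41. A t-based size, even for individual randomization, would be 43 for both.
- Proportions, unpooled, n = 10.469 × [p₁(1−p₁) + p₂(1−p₂)]/(p₁−p₂)²: physical activity 10.469 × 0.45/0.09 = 52.3; stress 10.469 × 0.2399/0.0441 = 57.0. Stated: 52 and 57. Pooled variances would give 57 and 61.
- Design effect: CV = 5.83/14 = 0.416; 1 + [(1 + 0.173) × 14 − 1] × 0.05 = 1.77, as stated.
- Losses: n × 1.2 + 14 gives 124.4, 100.4, 134.0 and 101.6, which round up to the stated 125, 101, 134 and 102. The single 14 shows that one cluster per arm is assumed lost, leaving 8 − 1 = 7 per arm and 21 in all.

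So the plan's arithmetic is consistent, and it uses normal quantiles throughout.

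**2. Degrees of freedom.** Three arms in one model: 21 − 3 = 18, or 17 with one more spent on company. A comparison using only two arms would have 14 − 2 = 12, taken here as a lower bound. Critical values at 0.05/3: 2.639 (18), 2.655 (17), 2.779 (12), against 2.394 for z.

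**3. Power at the sizes after the design effect.** Noncentrality = difference/(SD × √(2 × 1.77/n)). For sitting: 1/(1.4 × √(3.54/72)) = 3.22. The other three outcomes also give 3.22-3.23, so one table serves all four.

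| Reference distribution | alpha 0.05/3 | alpha 0.05 |
|---|---|---|
| z | 80% | 90% |
| t, 17-18 df | 71-72% | 86% |
| t, 12 df | 67% | 84% |

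**4. Power at 110 per arm after planned losses, alpha 0.05/3.** Analysed per arm: (110 − 14) × 0.8 = 76.8, or 7 × 14 × 0.8 = 78.4. After 20% loss the mean cluster size is 11.2, and the design effect falls to 1 + (1.173 × 11.2 − 1) × 0.05 = 1.61. Ranges cover both counts and 17-18 df.

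| Outcome | z, DE 1.77 | t, DE 1.77 | z, DE 1.61 | t, DE 1.61 |
|---|---|---|---|---|
| Sitting | 83% | 74-76% | 86-87% | 79-80% |
| Stroop | 82-83% | 74-75% | 86-87% | 78-80% |
| Physical activity | 71-72% | 62-63% | 76-77% | 67-68% |
| Stress | 67-68% | 58-59% | 72-73% | 63-64% |

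For physical activity the step from z to t costs about 8-9 points. The rest of its shortfall is already there with z, because 110 is below the stated need of 125. Stress has the same problem, with a stated need of 134.

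**5. Error rate if uncorrected z were used.** The two-sided tail of t with 18 df is 2.8% beyond 2.394 (nominal 1.67%) and 6.6% beyond 1.96 (nominal 5%). A simulation of 8,000 trials per scenario with a REML random-intercept model gave 2.6% and 6.4% for Wald z. With t critical values the level was held or slightly conservative: 1.1-1.5% and 4.1-4.7%. Simulated power for sitting, with 78 analysed per arm, was 80% with 18 df, 77% with 12 df and 86% with z.

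**6. Baseline adjustment.** The article gives no baseline correlation r, so this is an assumption. Scaling the variance by 1 − r² for sitting at n = 72 and alpha 0.05/3, over 12 to 18 df, gives 67-72% (r = 0), 72-76% (r = 0.3), 81-85% (r = 0.5) and 87-90% (r = 0.6).

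**The case against.** The other side has a good case on several points. Inflating an individual sample size by a design effect is a disclosed and referenced approach, and the sums are correct. The model includes baseline values, so a calculation without them is conservative; a correlation near 0.5 would restore 80%. At the 5% level of the Statistical analyses section, the stated sizes exceed 80% even with 12 degrees of freedom. For sitting time at 110 per arm, the post-loss design effect of 1.61 with 18 degrees of freedom brings power back to about 80%. All of this stands, and it limits the practical harm. It does not rescue the printed figure, which is tied to 0.017 and credits no baseline adjustment.

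Three stronger readings are tempting and are not supported:

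- *That both the power and the test level fail.* The article names multilevel modelling and no reference distribution, a detail commonly left to the analysis plan. With a small-sample method the level holds and power falls; with uncorrected z, power is kept and the level rises. These are alternatives.
- *That 12 degrees of freedom is the planned case.* One model with control as the reference group draws on all three arms, so 17-18 is the natural choice.
- *That the low power for physical activity is a small-cluster effect.* Only about 8-9 points are.

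**Conclusion.** The concern holds in this limited form. The 80% power stated at the 0.017 level does not follow for a test that respects about 7 clusters per arm. The stated sizes give about 71-72% (67% at 12 degrees of freedom). At the actual target of 110 per arm, sitting and Stroop have 74-76%, or 78-80% under the more favourable design effect, and physical activity has 62-68%.

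This rests on the plan's own ICC, cluster sizes, effects and losses, on a two-sided 0.05/3, on 17-18 degrees of freedom, and on no credit for baseline adjustment. The size of the problem depends on which significance level applies: at 5% the stated sizes keep 84-86%. Inflation of the error rate is conditional on a z-test that the article does not specify. The calculation should be corrected, but the point does not undermine the design.

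**What to change.** In the Sample size section, restate power with t-quantiles on cluster degrees of freedom for the 7 clusters per arm expected to remain. If baseline adjustment is to be credited, state the correlation assumed and where it comes from. Settle at the same time whether 0.017 or 5% applies, and use that level in both sections. No additional enrolment is asked for.

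For the analysis, name a small-sample method so that the stated level holds: Kenward-Roger or Satterthwaite degrees of freedom for continuous outcomes, and a cluster-level t or permutation test for binary outcomes. If the analysis plan already does this, only the power statement needs to change.

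The cost is one recalculation and a few lines of text. The downside is a less favourable stated power and slightly wider confidence intervals.
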